#### Quantification of RNA and Circular DNA Synthesis

The quantification stage serves to determine the RNA concentration in each sample in order to dilute them to the same concentration, which is 0.2 ng/µL. RNA quantification from each sample and control will be performed using the Qubit dsDNA HS kit (Q32851; Thermo Fisher Scientific). All samples from the whole genome amplification stage are vortexed and diluted by mixing 5 µL of the sample with 45 µL of double-distilled water to achieve a 1:10 dilution. Samples, controls, and the Qubit standard solution are placed in 500-µL tubes containing Qubit dsDNA reagent with specific volumes.

All samples are then vortexed, spun down, and incubated at room temperature for 2 minutes. The RNA quantification results are then used for circular DNA synthesis using the cDNA Taqman MicroRNA Reverse Transcription Kit (4366596; Thermo Fisher Scientific). The composition of the reagents used can be seen in Hidayati et al [10]. The master mix, containing the samples, is then incubated in a thermal cycler.

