#### Total RNA Isolation

RNA will be isolated from all samples using the RNeasy Mini Kit (Qiagen) following the kit’s manual instructions. Initially, β-mercaptoethanol and ethanol are added to Buffer RPE. Tissue samples are separated from RNAlater stabilization and then mixed with Buffer RLT. For tissue weighing 20-30 mg, 600 µL of Buffer RLT is added. Sample disruption and homogenization are performed using an ultrasonic disruptor tool for 20-40 seconds. The lysed samples are centrifuged at 17,000×g for 3 minutes, and the supernatant is collected for RNA extraction. Then, 70% ethanol, equal to 1× the lysate volume, is added and homogenized using a micropipette.

A total of 700 µL of the sample is transferred to a QIAamp spin column placed in a 2-mL collection tube and centrifuged at >8000×g for 1 minute. The supernatant is discarded, and the process is repeated by pairing a new 2-mL collection tube with the QIAamp spin column until all lysates, including precipitates, are processed. The supernatant and 2-mL collection tube are discarded. The QIAamp spin column is then transferred to a new 2-mL collection tube.

Buffer RW1 (700 µL) is added to the QIAamp spin column and centrifuged at >8000×g for 1 minute. The supernatant and 2-mL collection tube are discarded. This step is repeated with the addition of 500 µL of Buffer RPE. The QIAamp spin column is then combined with 500 µL of Buffer RPE and centrifuged at 17,000×g for 3 minutes, and the supernatant is transferred to a new 2-mL tube and centrifuged at 17,000×g for 1 minute. The QIAamp spin column is moved to a new 1.5-mL microcentrifuge tube, and 30-50 µL of RNase-free water is added directly to the QIAamp membrane, followed by centrifugation at >8000×g for 1 minute.

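### The step meant to equalise RNA input names a double-stranded DNA assay and a genome amplification stage that the workflow lacks, so as written it cannot equalise RNA

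*Protocol article*

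**What the plan says.** All of this stands in the protocol article, under Methods.

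- **Upstream step (Total RNA Isolation):** "RNA will be isolated from all samples using the RNeasy Mini Kit". The section describes lysis, column washing and elution, and no amplification of any kind.
- **Purpose of the next step (Quantification of RNA and Circular DNA Synthesis):** to "determine the RNA concentration in each sample in order to dilute them to the same concentration, which is 0.2 ng/µL".
- **Assay named for it:** "RNA quantification from each sample and control will be performed using the Qubit dsDNA HS kit".
- **Reagent in the tubes:** "Samples, controls, and the Qubit standard solution are placed in 500-µL tubes containing Qubit dsDNA reagent with specific volumes".
- **Material measured:** "All samples from the whole genome amplification stage are vortexed and diluted".
- **Pre-assay dilution:** tenfold in water, 5 µL made up to 50 µL.
- **Use of the reading:** it feeds the reverse transcription described in the same section.
- **Later normalisation:** Clinical Outcomes sets the five genes against β-actin, and the Data Analysis paragraph on Ct values applies the ΔΔCt method.

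**The concern.** The purpose, the assay and the sample source do not agree. The step exists to put RNA on a common concentration, but the assay is by its own name one for double-stranded DNA, and the material is attributed to a stage that copies DNA and has no place between RNA isolation and reverse transcription. The DNA assay is named once as the kit and once as the reagent, which makes a single typing slip less likely.

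Followed literally, there are two outcomes. If the RNA is clean, the DNA reading is close to zero and gives no usable dilution factor. If genomic DNA is carried over, specimens are equalised on that DNA. In either case the amount of RNA entering reverse transcription is unknown and can differ between the two specimens of a child. All five outcomes pass through this step, so the question is how much of an input difference survives into the normalised fold change.

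**Working it through.** **1. The one figure in the step that can be reproduced.** The pre-assay dilution is 5 µL in 5 + 45 = 50 µL, and 5/50 = 0.10. The stated 1:10 is correct. The problem lies in what is measured, not in this arithmetic.

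**2. The passages side by side.**

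| Element | Total RNA Isolation | Quantification section |
|---|---|---|
| Material | Total RNA from a column kit | Samples from whole genome amplification |
| Analyte | RNA | RNA by purpose, dsDNA by kit and reagent |
| Amplification before reverse transcription | None | Presupposed, described nowhere |

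The described sequence is RNA isolation, quantification, reverse transcription, qRT-PCR. Genome amplification is mentioned in no other section.

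**3. What an input difference does to the outcome.** The article gives neither RNA:DNA ratios nor amplification efficiencies, so these are assumptions:

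- k = ratio of RNA input between two specimens, taken as 2 or 4
- a_T = amplification factor per cycle for the target, taken as 2.0, 1.95 or 1.9
- a_R = amplification factor for β-actin, taken as 2.0

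Raw shift in the β-actin Ct = ln k / ln a_R. For k = 2 this is 1.00 cycle, and for k = 4 it is 2.00 cycles.

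Residual after normalisation: d = ln k / ln a_T − ln k / ln a_R. ΔΔCt converts it to a spurious fold change of 2^d.

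| k | a_T = 2.0 | a_T = 1.95 | a_T = 1.9 |
|---|---|---|---|
| 2 | d = 0.00, 1.00-fold | d = 0.04, 1.03-fold | d = 0.08, 1.06-fold |
| 4 | d = 0.00, 1.00-fold | d = 0.08, 1.05-fold | d = 0.16, 1.12-fold |

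Worked example, k = 4 and a_T = 1.9: 1.386/0.642 − 1.386/0.693 = 2.16 − 2.00 = 0.16 cycle, and 2^0.16 = 1.12. As a stress case, k = 10 with a_T = 1.9 gives d = 0.27 and 1.20-fold.

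**4. Direction.** When the target amplifies less efficiently than β-actin, the specimen with more RNA appears to express the target more strongly. If the input ratio is unrelated to side, this falls on ventral and dorsal specimens alike and adds variance. Only an input ratio that differs on average by side would shift the ventral-dorsal contrast.

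**The case against.** The strongest defence is that raw Ct is not the outcome. Expression is taken relative to β-actin, and ΔΔCt exists to remove input differences. With equal efficiencies the residual is nil at any input ratio, and with modestly unequal ones it is a few per cent to about 12%. This stands, and it limits the severity. It does not rescue the step: the protocol sets equal RNA concentration as a separate aim, and the named assay cannot deliver it.

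It may also be said that the paragraph was carried over from another workflow and that the laboratory in fact measures RNA. That is possible, and the article cannot settle it. The text still contradicts itself and cannot be followed for its stated purpose.

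A reader might go further in three ways that the document does not support.

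- **That the ventral-dorsal comparison is systematically biased.** This needs DNA carry-over or cell content to differ by side, and nothing in the article says so. Under Randomization and Blinding, the laboratory assistant does not know the side, which makes differential handling unlikely.
- **That 0.2 ng/µL is a target taken from a DNA protocol.** The surrounding wording suggests it, but the article gives no source for the figure.
- **That 0.2 ng/µL of RNA leaves too few transcripts per well for stable Ct values.** The article gives neither transcript abundance nor reaction volume, so copies per well cannot be derived. That worry also concerns samples whose RNA truly is at 0.2 ng/µL, which is a different situation from the one here.

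**Conclusion.** The contradiction is real. The section states an RNA purpose, names a dsDNA kit and reagent, and cites a sample source that the workflow does not contain. If carried out as written, RNA input to reverse transcription is not equalised between ventral and dorsal specimens.

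The expected effect on the normalised outcomes is small: about 1.00- to 1.12-fold for assumed input differences of 2- to 4-fold and target amplification factors of 1.9 to 2.0 against 2.0 for β-actin. It is mainly added noise unless carry-over differs by side. The finding does not show that the fold changes would be invalid. It should be corrected because the step is wrong as written, every outcome depends on it, and the correction is cheap.

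**What to change.** In Quantification of RNA and Circular DNA Synthesis:

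1. Name an RNA-specific fluorometric assay in place of the dsDNA kit and the dsDNA reagent.
2. Replace the reference to whole genome amplification with the total RNA obtained in the preceding section.
3. State a common RNA input to reverse transcription for both specimens of a child, and confirm 0.2 ng/µL as an RNA concentration or revise it.

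The cost is a reagent swap and one corrected paragraph. If laboratory practice already differs from the text, only the paragraph changes. The design, the tissue sampling and the number of specimens are unaffected.

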**Objective:**

The study’s aim is to investigate the differences in messenger RNA (mRNA) expression of fibulin-1, elastin, matrix metalloproteinase-1, basic fibroblast growth factor, and α-smooth muscle actin between the ventral and dorsal tunica dartos in patients with hypospadias and chordee.

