### Clinical Outcomes

The clinical outcomes measured in this study are as follows:

Expression of fibulin-1 mRNAExpression of elastin mRNAExpression of MMP-1 mRNAExpression of bFGF mRNAExpression of α-SMA mRNA

The clinical outcomes will be measured from differences in mRNA expression from both the dorsal and ventral aspects of the tunica dartos excised during urethroplasty. A positive control gene for both dorsal and ventral tissues will also be measured in subsequent analyses. The expression levels of the 5 genes will be assessed relative to the housekeeping gene β-actin using fold change values.

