#### Expression Quantification Using a Real-Time Quantitative Reverse Transcription–Polymerase Chain Reaction Machine

A real-time quantitative reverse transcription–polymerase chain reaction (qRT-PCR) machine will be used to perform the qRT-PCR amplification using the primary sequences in Table 1.

The machine monitors fluorescence levels after each PCR cycle to track the amount of amplified DNA in real time.

**Table 1 table1:** Primary sequences of the genes used in the study.

Gene	Nucleotide code	Primary sequence (5’-3’)
Fibulin-1	NM_006486.3	F^a^: GATGGTGTCTCCTGTGAAGATG R^b^: TGATGCATGTATGCCCGATAG
Elastin	NM_000501.4	F: CTGCAAAGGCAGCCAAATAC R: CACCAGGAACTAACCCAAACT
MMP-1^c^	NM_002421.4	F: GCCTTCCAACTCTGGAGTAATG R: GAATGGGAGAGTCCAAGAGAATG
bFGF^d^	NM_001361665.2	F: TGAAACGAACTGGGCAGTATAA R: TTGACCTGACTGTGGAAGAAC
αSMA^e^	NM_001613.4	F: GACCCTGAAGTACCCGATAGA R: CTCAGCAGTAGTAACGAAGGAATAG

^a^F: forward.

^b^R: reverse.

^c^MMP-1: matrix metalloproteinase-1.

^d^bFGF: basic fibroblast growth factor.

^e^α-SMA: α-smooth muscle actin.

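### The only reverse transcription kit named is a MicroRNA kit, although all five outcomes are mRNAs, and no mRNA priming is stated

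*Protocol article*

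**What the plan says.** For the two aspects of the tunica dartos, the Objective gives this aim: "investigate the differences in messenger RNA (mRNA) expression of fibulin-1, elastin, matrix metalloproteinase-1, basic fibroblast growth factor, and α-smooth muscle actin". The Clinical Outcomes section lists those same five mRNAs as the outcomes and names β-actin as the reference gene.

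The section on RNA quantification and cDNA synthesis describes "circular DNA synthesis using the cDNA Taqman MicroRNA Reverse Transcription Kit", with catalogue number 4366596. On what goes into the reaction it says only "The composition of the reagents used can be seen in" a cited study.

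The next section states that a real-time machine "will be used to perform the qRT-PCR amplification using the primary sequences in Table 1". Table 1, headed "Primary sequences of the genes used in the study", gives each of the five genes an NM_ code and a forward and reverse primer. The first fibulin-1 primer, for example, is "GATGGTGTCTCCTGTGAAGATG". The Ct values are then normalised to the housekeeping gene and analysed by the ΔΔCt method.

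**The concern.** Reverse transcription decides which RNA becomes template for the PCR. The article names a product labelled for one class of RNA (microRNA), while its outcomes and PCR primers belong to another (mRNA). Nothing in the text joins the two: there is no statement that the kit was modified, and none on how the reaction is primed.

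The whole study passes through this step. If the mRNAs of interest were not copied, or only incidentally, Ct values for the targets and for β-actin would be late, noisy or absent, and the ventral–dorsal contrast would not measure mRNA expression. The tissue is also limited. It comes from children aged 6–18 months at urethroplasty, the RNA isolation section works with 20–30 mg, and insufficient tissue is an exclusion criterion. A specimen spent on an unsuitable reaction may not be replaceable.

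**Working it through.** The plan gives no figure to reproduce here, so the check sets the sections side by side.

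1. **What must be measured.** Objective and Clinical Outcomes: five outcomes, of which 5 are mRNAs and 0 are microRNAs.
2. **What the PCR is built to amplify.** Table 1: five targets, of which 5 are protein-coding genes with NM_ codes and 0 are microRNAs. The table lists forward and reverse PCR primers only, with no reverse transcription primer.
3. **What makes the template.** The cDNA synthesis section: one product named, labelled for microRNA. This is the only mention of microRNA in the article.
4. **How the reaction is primed.** Not stated. Random, oligo-dT, gene-specific and microRNA-specific priming are all left open, and the composition is referred to a cited study.
5. **How much depends on the step.** Five targets plus β-actin make 5 + 1 = 6 transcripts. With two sides per child, that is 6 × 2 = 12 Ct values per child before any replicates, and all 12 come from this reverse transcription.
6. **Whether normalisation could repair a failure.** For each gene and side, ΔCt = Ct(target) − Ct(β-actin). Taking the dorsal side as calibrator for illustration (the article does not name one), ΔΔCt = ΔCt(ventral) − ΔCt(dorsal). Each ΔΔCt uses four Ct values, all from the same step. If any is undetermined, ΔΔCt cannot be formed. If they are erratic, the subtraction carries the error forward. Normalisation allows for differing amounts of input, not for a template that was not made.

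Two cases remain:

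- **The kit is used with microRNA-specific priming.** Such primers are not designed for the five mRNAs or for β-actin, so cDNA for these six would not be expected. This is an assumption about the reaction; the article neither confirms nor excludes it.
- **mRNA priming is added, or a different kit is used.** Suitable cDNA can be produced, but the method as published is then not the method used and cannot be reproduced from the text.

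The documents do not show which case applies. Both require a change to the section.

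**The case against.** The strongest reply is that a kit's name does not settle what the reaction yields. That depends on the primers put into it. The article sends the reader elsewhere for the composition, and the kit's contents are not described in the documents. A condensed article may leave priming detail to a fuller protocol, so its absence alone is no evidence of wrong priming. A feasibility pilot has also been running since August 2023, and a complete failure to amplify could show there.

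Much of this stands. A reader might infer that the named step cannot produce the cDNA that the Table 1 primers need. The documents do not support that: nothing says so, and with random, oligo-dT or gene-specific primers it could. A reader might also infer that any signal left would come from genomic DNA, because the same section names a dsDNA kit for RNA quantification. That would need facts on DNA carry-over and primer placement that the article does not give. The dsDNA kit and the mention of a whole genome amplification stage fit text carried over from another assay, but they do not prove it. The pilot is not said to test amplification.

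The reply does not remove the mismatch. The objection to missing detail does not apply to detail that was given: the article states a product and a catalogue number, and these do not fit its own outcomes and primers. A fuller protocol could explain the choice, but the published statement would still need explaining or correcting.

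**Conclusion.** The point holds as an internal contradiction in a stated method. The one reverse transcription product named is labelled for microRNA, all five outcomes and all five primer pairs are for mRNA, and no priming is given that reconciles them. Its reach is complete, since 12 of 12 Ct values per child depend on the step. That figure counts what is exposed and does not estimate lost signal. Loss of signal is conditional on microRNA-specific priming, which is an assumption. In the other case the defect is a wrongly reported method. The documents establish neither assay failure nor genomic-DNA signal.

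The term circular DNA, used where complementary DNA is meant, is a slip of wording. It changes no measurement and adds nothing to the weight of the point.

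**What to change.** In the section on RNA quantification and cDNA synthesis, do one of two things:

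- replace the named product with a reverse transcription kit for mRNA or total RNA; or
- if the named kit is kept, state the priming (random, oligo-dT or gene-specific) that yields cDNA for the five Table 1 targets and β-actin.

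Then confirm on pilot RNA that all six transcripts amplify before the remaining tissue is used. As an editorial point only, change circular DNA to complementary DNA in the heading and text.

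The cost is one corrected paragraph, a reagent change if the first option is taken, and a brief check on pilot RNA. Controls without reverse transcriptase and same-run processing of a child's two specimens are good practice, but are not needed to settle this point.

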#### Expression Quantification Using a Real-Time Quantitative Reverse Transcription–Polymerase Chain Reaction Machine

A real-time quantitative reverse transcription–polymerase chain reaction (qRT-PCR) machine will be used to perform the qRT-PCR amplification using the primary sequences in Table 1.

The machine monitors fluorescence levels after each PCR cycle to track the amount of amplified DNA in real time.

**Table 1 table1:** Primary sequences of the genes used in the study.

Gene	Nucleotide code	Primary sequence (5’-3’)
Fibulin-1	NM_006486.3	F^a^: GATGGTGTCTCCTGTGAAGATG R^b^: TGATGCATGTATGCCCGATAG
Elastin	NM_000501.4	F: CTGCAAAGGCAGCCAAATAC R: CACCAGGAACTAACCCAAACT
MMP-1^c^	NM_002421.4	F: GCCTTCCAACTCTGGAGTAATG R: GAATGGGAGAGTCCAAGAGAATG
bFGF^d^	NM_001361665.2	F: TGAAACGAACTGGGCAGTATAA R: TTGACCTGACTGTGGAAGAAC
αSMA^e^	NM_001613.4	F: GACCCTGAAGTACCCGATAGA R: CTCAGCAGTAGTAACGAAGGAATAG

^a^F: forward.

^b^R: reverse.

^c^MMP-1: matrix metalloproteinase-1.

^d^bFGF: basic fibroblast growth factor.

^e^α-SMA: α-smooth muscle actin.

#### Data Analysis

The amplification curve data will then be analyzed to determine the cycle threshold (Ct) value. The Ct values are then normalized to that of the housekeeping gene to calculate the relative gene expression using the ΔΔCt method.

### Data Analysis

The data to be collected in this study include clinical characteristics such as age, height, weight, BMI, comorbidities, and delivery history, accompanied by mRNA expression from both the dorsal and ventral sides of the tunica dartos tissue.

All quantitative data obtained from this research will be analyzed using SPSS (version 25.0; IBM Corp) software. The normality of all numeric data will be tested using the Kolmogorov-Smirnov test. Numeric data will be presented as mean (SD) for normally distributed data and median (range) for nonnormally distributed data.

If the obtained data are normally distributed, an independent 2-tailed *t* test will be performed. Meanwhile, nonnormally distributed data will be tested using the Mann-Whitney *U* test to determine gene expression differences between research groups. The quantification of gene expression is expressed as fold change, compared to the housekeeping gene used in the study.

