### Study Process and Data Collection

#### Specimen Collection

In this study, tissue samples from the dorsal and ventral sides of the tunica dartos will be obtained from patients with hypospadias and chordee. Ventral tunica dartos samples will be taken from each patient by the researcher as the performing operator, ensuring that the size and location of collection are standardized across all patients. The collected portions are shown in Figure 1.

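### A Kolmogorov-Smirnov test of site values chooses the summary and one of two unpaired tests, although the comparison is within child; one paired log2 analysis should be fixed for all five genes

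*Protocol article*

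**What the plan says.** The main Data Analysis section of the protocol article sets a two-stage rule. First, "The normality of all numeric data will be tested using the Kolmogorov-Smirnov test". The outcome decides the description: "Numeric data will be presented as mean (SD) for normally distributed data and median (range) for nonnormally distributed data". It also decides the test: "If the obtained data are normally distributed, an independent 2-tailed *t* test will be performed", while "nonnormally distributed data will be tested using the Mann-Whitney *U* test to determine gene expression differences between research groups". On scale, the same section adds: "The quantification of gene expression is expressed as fold change, compared to the housekeeping gene used in the study". The shorter Data Analysis paragraph under Study Process and Data Collection says that Ct values are "normalized to that of the housekeeping gene to calculate the relative gene expression using the ΔΔCt method".

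On design, Specimen Collection says that "tissue samples from the dorsal and ventral sides of the tunica dartos will be obtained from patients with hypospadias and chordee", and Clinical Outcomes says: "The clinical outcomes will be measured from differences in mRNA expression from both the dorsal and ventral aspects of the tunica dartos excised during urethroplasty". The Discussion acknowledges that no tissue from healthy children is included. The only comparison is therefore between two sites in the same children, for five genes.

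The article gives no sample size, significance level, expected effect or SD. It does not say which variant of the Kolmogorov-Smirnov test is meant.

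**The concern.** Three features of the rule do not fit the design.

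- **Quantity.** For matched specimens, the inference rests on the distribution of the within-child difference. A check on the values as collected can fail when the differences are well behaved, and can pass when they are not. Whatever it finds, the rule leads only to tests for independent groups.
- **Scale.** A fold change from the ΔΔCt method is a power of 2 of a Ct difference, so it is typically right-skewed. The log2 scale is known in advance to be the natural one, and no test is needed to find it.
- **Consistency.** If the rule is applied to each variable, genes with the same underlying distribution can receive different tests and summaries by chance. The five results would then be hard to set side by side.

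At stake are the power to detect a ventral-dorsal difference and the comparability of the five gene results.

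**Working it through.** The article has no figure to reproduce. The following inputs are assumptions: 10 to 50 children, two-sided level 0.05, log2 SD per site 0.5 to 1.5, within-child correlation ρ from 0 to 0.7, and a log2 shift of 0 or 0.7. Taken from the article are the two tests, the fold-change scale, two sites per child and five genes. Power and error rates were simulated with 10,000 to 20,000 replicates (3,000 for Shapiro-Wilk). The rule was read as Mann-Whitney if either site is rejected, otherwise the independent t test, both on fold changes.

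**1. How often the normality test rejects skewed fold changes, 2^N(0, SD)**

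| Test, log2 SD | n=10 | n=20 | n=30 | n=50 |
|---|---|---|---|---|
| Lilliefors-corrected, 0.5 | 0.11 | 0.20 | 0.27 | 0.43 |
| Lilliefors-corrected, 1 | 0.28 | 0.54 | 0.73 | 0.92 |
| Lilliefors-corrected, 1.5 | 0.48 | 0.81 | 0.95 | 1.00 |
| Uncorrected, 1 | 0.006 | 0.055 | 0.14 | 0.37 |
| Shapiro-Wilk, 1 | 0.38 | 0.75 | 0.92 | 0.99 |

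**2. Different tests for different genes.** Let q be the rejection rate per site. With independent sites, the chance of switching to Mann-Whitney is p = 1 − (1 − q)². For five independent genes with the same distribution, the chance that they do not all get the same test is 1 − p⁵ − (1 − p)⁵. At log2 SD 1 with the Lilliefors correction:
- n=10: p = 1 − 0.72² = 0.48, giving 0.94
- n=20: p = 1 − 0.457² = 0.79, giving 0.69
- n=30: p = 1 − 0.269² = 0.93, giving 0.31 (0.32 when simulated directly)

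With a true shift of 0.7, the t test and Mann-Whitney disagree on significance in 10% to 22% of samples.

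**3. Site values against differences.** In a constructed example, a skewed child effect is shared by both sites and normal noise is added at each. The site values are rejected in 34%, 60% and 78% of samples at n = 10, 20 and 30. The within-child differences are normal and are rejected in 5%.

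**4. Effect on the comparison (log2 SD 1, n = 10 / 20 / 30)**

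| ρ | Type I error, stated rule | Power, stated rule | Power, paired t on log2 |
|---|---|---|---|
| 0 | 0.051 / 0.056 / 0.045 | 0.30 / 0.56 / 0.73 | 0.29 / 0.55 / 0.74 |
| 0.3 | 0.026 / 0.024 / 0.020 | 0.28 / 0.58 / 0.77 | 0.39 / 0.71 / 0.88 |
| 0.5 | 0.011 / 0.010 / 0.007 | 0.26 / 0.59 / 0.80 | 0.51 / 0.84 / 0.96 |
| 0.7 | 0.002 / 0.002 / 0.001 | 0.24 / 0.63 / 0.86 | 0.72 / 0.97 / 1.00 |

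The paired test's type I error is 0.046 to 0.053 throughout. Its power can be checked directly. The SD of the difference is √(2(1 − ρ)), so the noncentrality is 0.7√n/√(2(1 − ρ)). At ρ = 0.5 this is 0.7√n = 2.21, 3.13 and 3.83, and the noncentral t distribution gives 0.51, 0.84 and 0.96.

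**5. Where the loss comes from.** At ρ = 0, the rule and the paired log2 test differ by at most about 0.013 in power, and the rule holds its level. Gate and scale together therefore cost almost nothing here. The gap opens as ρ rises, which is the mark of ignored pairing. An unpaired test uses a standard error too large by a factor 1/√(1 − ρ). At ρ = 0.5 and in large samples on the log2 scale, its actual level is 2Φ(−1.96/√0.5) = 2Φ(−2.77) = 0.006, in line with the simulated 0.007 to 0.011.

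**The case against.** The strongest defence is that the rule and both branches are written down in advance, so the analyst has no open choice, and that site values are what one would examine before an independent t test. The first part stands: this is not undisclosed discretion. The second shows that the gate's fault follows from the unpaired tests. It does not rescue the gate, because pairing the two tests and keeping the gate would still allow the genes to be analysed differently.

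A reader might infer more than the article supports:

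- *That the normality test has little power at the likely sample size.* No sample size is stated. Power is low for few children, mild skew or the uncorrected version. It is not low at 30 children with log2 SD 1 and the Lilliefors correction (0.73). The article does not say which version applies.
- *That the pretest makes the results unreliable.* With uncorrelated sites the two-stage type I error stays at 0.045 to 0.056. With correlated sites the error is conservative, and lack of pairing causes it.
- *That the choice is certainly made gene by gene, on untransformed fold changes.* Both are natural readings, but neither is written. The fold-change sentence may describe reporting only. If the tests were run on ΔCt, the skewness argument would weaken and the pairing argument would stand.
- *That the rule is defective because it does not cover one site passing and the other failing.* A condensed article commonly leaves such detail to the full protocol or analysis plan.

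**Conclusion.** The point holds as a mismatch between the stated rule and the design. A normality test of the observed values should not select the analysis of a within-child comparison, and neither test it can select is paired. Most of the cost lies in the unpaired tests: at ρ = 0.5 and a log2 shift of 0.7, power falls short by 0.51 − 0.26 = 0.25, 0.84 − 0.59 = 0.25 and 0.96 − 0.80 = 0.16 at 10, 20 and 30 children. The gate's own harm is inconsistency between genes, not loss of error control. The inconsistency figures assume variable-by-variable use, independent genes and sites, and the Lilliefors correction. All sizes rest on assumed numbers of children, SDs and correlations, because the article gives none. If the sites are uncorrelated within a child, the power loss disappears and only the inconsistency remains.

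**What to change.** Delete the normality gate and name one analysis for all five genes:

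- **Primary:** a paired t test with 95% confidence interval on the within-child difference in ΔCt (ventral minus dorsal, log2 scale). Report it back-transformed as a geometric mean ratio, 2 to the power of minus the mean difference.
- **Sensitivity:** a Wilcoxon signed-rank test on the same differences, always run.
- **Description:** the same summaries for every gene, with a Q-Q plot of the differences that does not alter the analysis.

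The cost is wording only. If the within-child correlation is near zero and there are few children, the paired test gives up a little power (about 0.28 to 0.29 against 0.30 at n=10).
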